### Randomization and allocation concealment

After baseline assessment, eligible participants will be randomly assigned to three groups (Tai Chi Chuan group (TCC), unstable resistance training group (URT), or Tai Chi Chuan combined with unstable resistance training group (T + URT)) in a 1:1:1 ratio using simple randomization. The randomization sequence will be generated by an independent statistician using SPSS (version 25.0, IBM Corp., Armonk, NY, USA). Allocation details will be sealed in sequentially numbered, opaque envelopes. A research assistant not involved in outcome assessment will open the envelopes after baseline testing, just before the first intervention session.

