### Sample size

The sample size will be estimated using PASS 15.0 software. Knee extensor peak torque will be selected as the primary outcome for sample size calculation. Based on relevant preliminary and published experimental data, the expected mean and standard deviation of post-intervention knee extensor peak torque in the three groups will be used to estimate an effect size of Cohen’s *f* = 0.55. With a two-sided alpha level of 0.05, statistical power of 0.90, and one-way analysis of variance for three-group comparison, the minimum required sample size is 16 participants per group. Allowing for an anticipated dropout rate of approximately 15%, 19 participants will be enrolled in each group, yielding a total sample size of 57 participants (32).

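### Simple randomisation of 57 participants cannot be relied on to give the stated 19 per group; the allocation method and the sample-size statement need to be reconciled

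*Protocol article*

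**What the plan says.** Protocol article, Randomization and allocation concealment: after baseline assessment, participants are assigned "in a 1:1:1 ratio using simple randomization". "The randomization sequence will be generated by an independent statistician using SPSS", and the allocations are held in numbered opaque envelopes that are opened after baseline testing, just before the first session. The section mentions no blocks, strata or fixed group totals.

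Protocol article, Sample size: "the minimum required sample size is 16 participants per group", obtained "With a two-sided alpha level of 0.05, statistical power of 0.90", an effect size of Cohen's f = 0.55 and "one-way analysis of variance for three-group comparison". After an allowance for about 15% dropout, "19 participants will be enrolled in each group, yielding a total sample size of 57 participants".

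**The concern.** Under simple randomisation each participant is assigned independently with probability 1/3 per group, so the group sizes are random. The Sample size section treats them as fixed. Both statements hold together only by luck.

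Three things are at stake. The first is the promised group size. The second is the dropout reserve, which is the step from 16 to 19 in each group and can be used up by chance before anyone leaves. The third is the precision of the pairwise comparisons: the main hypothesis sets the combined programme against each single modality, so a small group matters more there than in an overall test.

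**Working it through.** **Inputs.** From Sample size: 16 per group required, 15% dropout, 19 per group, 57 in total, f = 0.55, two-sided alpha 0.05, power 0.90. From Randomization and allocation concealment: simple allocation, probability 1/3 per group.

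**1. The plan's own figures.** Power of the one-way ANOVA from the noncentral F distribution, with noncentrality N × f² and degrees of freedom 2 and N − 3:
- 15 per group: power 0.9001
- 16 per group: power 0.920
- 19 per group: power 0.960

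The stated 16 is one more than the smallest number that reaches 0.90. Dropout: 16 / 0.85 = 18.8, rounded up to 19; 3 × 19 = 57. The sample size reproduces.

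**2. Group sizes under simple randomisation.** The sizes follow a trinomial distribution (57; 1/3, 1/3, 1/3). One group has mean 57/3 = 19 and SD √(57 × 1/3 × 2/3) = 3.56. The chance of exact balance is 57! / (19!³ × 3⁵⁷) = 0.0143. Enumerating every split gives:

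| Event at randomisation | Probability |
|---|---|
| Exactly 19/19/19 | 1.4% |
| Some group below 19 | 98.6% |
| Some group below 16 | 47% |
| Smallest group 12 or fewer | 9.1% |
| Largest minus smallest 10 or more | 27% |

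The expected smallest group is 15.4, and the median gap between largest and smallest is 7.

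**3. Pairwise precision.** For a given pair, the variance relative to the balanced design is (1/n₁ + 1/n₂) / (2/19). Over all splits its mean is 1.039 and its 90th percentile is 1.1875. So the variance is about 4% larger on average, and about 19% or more larger in one allocation in ten.

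**4. Overall power.** The group means are held fixed at f = 0.55 and alpha at 0.05. Two patterns of means were tried, because the article does not give the means: one group different from two equal ones, and three equally spaced.

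| | Balanced | Simple randomisation, average | Splits with power below 0.90 |
|---|---|---|---|
| 57 analysed | 0.960 | 0.953 | 1.7% to 3.0% |
| 48 analysed | 0.920 | 0.909 to 0.910 | 31% to 33% |

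With 57 analysed, among the splits that have a group below 16, power is below 0.90 in only 3.6% to 6.4%.

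**5. The dropout reserve.** For illustration, assume each participant drops out independently with probability 0.15. All three groups then finish with at least 16 in 32% of trials that start at 19/19/19, and in 7% of trials under simple randomisation.

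**The case against.** The strongest defence is that nothing here threatens validity. Simple randomisation is unbiased, the 1:1:1 ratio is met as a probability, the intention-to-treat set takes everyone as allocated, and one-way ANOVA does not need equal groups. All of that stands.

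A reader might infer from the 47% that the trial loses its 90% power in nearly half of allocations. The documents' own figures do not support this. Sixteen per group is a planning number for a balanced design, not a floor. When one group is small the others are larger, and with 57 analysed, power falls below 0.90 in only about 2% to 3% of allocations.

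The authors may also have used the term loosely for a shuffled list of 19 codes per group. A sequence made in advance and sealed in envelopes would fit that, and there would then be no imbalance. The text does not say so, however, and as written it describes unrestricted allocation.

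A reader might also suppose that staff will close a group once it reaches 19, which would make the last assignments predictable. The article describes no such procedure. Because the envelopes are opaque and opened only after baseline testing, predictability would in any case have limited effect.

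**Conclusion.** The point holds as an inconsistency with a modest cost. The allocation method and the group sizes in the same article agree in only 1.4% of allocations, and the per-group minimum of 16 is already missed somewhere at randomisation in 47%. What suffers is the stated group sizes, the per-group dropout reserve and pairwise precision. Overall power falls only slightly on average.

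The group-size and variance figures rest on the literal reading of simple randomisation and on exactly 57 randomised. The power figures also rest on the plan's f = 0.55, alpha of 0.05 and the two assumed patterns of means. The change is worth making because it is nearly free and the imbalance brings nothing in return.

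**What to change.** In Randomization and allocation concealment, replace simple randomisation with a restricted scheme that yields 19 per group. Either of these will do:
- permuted blocks of varying, undisclosed size, each a multiple of 3 and together summing to 57; or
- if the whole cohort is allocated at one time, a random permutation of 57 codes, 19 for each group.

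The independent statistician and the opaque envelopes stay; only the list changes. With 57 randomised, every group then starts at 19, and 15% dropout leaves an expected 19 × 0.85 = 16.15 per group, which meets the stated minimum on average. The cost is slight predictability at block ends, limited by varying and undisclosed block sizes and by opening envelopes only after baseline testing.

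If the list is already of this kind, one corrected sentence is enough. If simple randomisation is kept, the Sample size section should give 19 per group as an expected size only.

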### Blinding

Because of the clear operational differences among the exercise interventions, participants and instructors cannot be blinded. However, outcome assessors, data entry personnel, and statistical analysts will be blinded to group allocation. Group codes will be retained until the main statistical analysis has been completed. This approach is intended to reduce measurement and analysis bias while preserving the feasibility of the intervention.

### Interventions

All groups will train for 8 weeks, three sessions per week, 60 min per session. Each session will include a standardized 10-min warm-up and a standardized 10-min cool-down. Exercise intensity is designed based on the progressive overload, specificity, and neuromuscular adaptation principles of sports coaching, and monitored using a Polar heart rate monitor. Target intensity will gradually increase from approximately 50% of maximum heart rate in week 1 to approximately 60% of maximum heart rate from week 3 onward. There are no differences between the prescribed intensity and the actual training performed, as real-time heart rate monitoring and on-site instructor supervision ensure strict implementation of the intensity protocol. Maximum heart rate will be estimated as 220 minus age. Training instructors will record attendance, heart rate, adverse events, and protocol deviations after each session (Table 2) (21, 22).

**Table 2 tab2:** Standardized warm-up, cool-down, intensity monitoring and safety supervision protocol.

Component	Protocol
Warm-up	Deep breathing for 1 min; dynamic stretching of upper limbs and trunk for 3 min; static stretching of lower-limb muscles for 3 min, focusing on quadriceps, hamstrings, and gluteal muscles; knee rotations and ankle flexion-extension for 3 min.
Cool-down	Whole-body static stretching for 6 min followed by slow walking for 4 min.
Intensity monitoring	Heart rate monitored in real time; intensity progressed from 50% HRmax during early adaptation to 60% HRmax during later weeks; HRmax calculated as 220 - age.
Safety supervision	Sessions supervised by trained instructors; movement quality, fatigue, dizziness, pain, and injury signs monitored continuously.

### Tai chi Chuan group

Participants allocated to the TCC group will receive 24-form simplified Tai Chi Chuan training using a phased learning and training model. All exercises will be performed on stable ground without external resistance equipment (Table 3 and Figure 2). Continuous practice of the 24-form Tai Chi Chuan for approximately 8 min has been shown to maintain steady-state activation of the muscles around the knee (especially the vastus medialis and biceps femoris) and sustained proprioceptive demand, without excessive fatigue that would compromise movement quality (18). Furthermore, the present study adopts a protocol of 7–8 sets per session, with a total training volume of approximately 60 min, which is consistent with effective intervention protocols in young adults (23).

**Table 3 tab3:** Phased training protocol for the Tai Chi Chuan group.

Phase	Weeks	Training content	Training requirements
Learning phase	1–2	Explanation of basic Tai Chi Chuan movements, body weight shifting, breathing methods, and segmented learning of the first 12 movements.	One to two movements taught per day; demonstration videos provided after each session; participants required to independently complete segmented movements.
Consolidation phase	3–4	Completion of the full 24-form Tai Chi Chuan routine and repeated practice to correct movement standardization.	Fluid movements, stable body weight distribution, coordinated breathing, and consistent pace of approximately 8 min per set.
Training phase	5–8	Continuous practice of the full 24-form routine, approximately 8 min per set, 7–8 sets per session, with 1-min rest intervals.	Maintain 50–60% HRmax; emphasize proper form, knee muscle activation, and proprioceptive awareness.

**Figure 2 fig2:**
[figure not shown]
Training images for the three groups. Column A displays training photographs of the TCC group; Column B displays training photographs of the URT group; Column C displays training photographs of the T + URT group.

### Unstable resistance training group

Participants allocated to the URT group will receive lower-extremity unstable resistance training using balance pads and wobble boards. The protocol will progress from bodyweight to light external resistance, targeting the knee flexor-extensor muscle groups and core stabilizing muscles (Table 4 and Figure 2). According to ACSM guidelines, a 30-s contraction time (approximately 12–15 repetitions) on unstable surfaces is sufficient to induce strength-endurance adaptations without early fatigue-induced postural sway, and a 1:2 work-to-rest ratio (30s work / 60s rest) maintains movement quality and reduces injury risk (24, 25).

**Table 4 tab4:** Phased training protocol for the unstable resistance training group.

Phase	Weeks	Training content	Load/rest	Training requirements
Adaptation	1–2	Wall-assisted squats on a balance pad; lunges on a balance pad; static heel raises on a balance pad; single-leg standing on a balance pad.	30 s per set, 3 sets, 60-s rest between sets.	Maintain stable posture; avoid knee hyperextension or abduction; focus on deep muscle activation.
Improvement	3–4	Dynamic half-squats on a balance pad; dynamic lunges on a balance pad; single-leg touch-down exercise on a balance pad; static half-squats on a wobble board.	30 s per set, 3 sets, 60-s rest between sets.	Maintain center-of-gravity control; coordinate slow knee flexion-extension with movement rhythm.
Consolidation	5–8	Static knee squats while holding a medicine ball on a balance pad; weighted reverse lunges on a wobble board with 1–2 kg dumbbells; weighted heel raises on a balance pad with 1–2 kg dumbbells.	20 s static squats per set or 15 repetitions per set; 3 sets per movement; 60-s rest between sets.	Apply light external resistance; maintain standardized movement; avoid excessive swaying; enhance knee strength control.

### Combined intervention group

Participants allocated to the T + URT group will complete 30 min of Tai Chi Chuan followed immediately by 30 min of unstable resistance training during each 60-min session. The first 30 min will include 3–4 sets of the complete 24-form Tai Chi Chuan routine. The subsequent 30 min will include the unstable resistance exercises corresponding to the current phase of the URT protocol. No additional rest interval will be inserted between the Tai Chi Chuan and resistance components. The overall training intensity will be maintained at 50–60% HRmax.

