To our knowledge, no three-arm RCT has directly compared Tai Chi Chuan combined with unstable resistance training versus each intervention alone in sedentary female college students, despite prior work examining Tai Chi with instability, vibration, or core training in other populations or designs (18, 42). Existing Tai Chi studies have largely focused on older adults or clinical populations, with limited data on muscle strength gains in young females (12, 43). Unstable resistance training studies have mainly involved healthy or athletic populations, rarely examining the hamstring-to-quadriceps ratio or eyes-closed dynamic balance (39, 44, 45). This protocol fills this gap by evaluating a central-peripheral complementary approach. Conversely, if no added benefit is found, this would suggest excessive neuromuscular demand without further gain — an equally informative finding. By comparing three arms, this trial will provide the first high-level evidence on whether combining these two training philosophies yields synergistic effects on knee function and dynamic balance in young sedentary women.

This protocol includes several methodological strengths. First, the randomized three-arm design allows direct comparison between two single-modality interventions and their combination. Second, objective laboratory measures will be used for both strength and balance outcomes. Third, blinded outcome assessment and statistical analysis will reduce bias. Fourth, both intention-to-treat and per-protocol analyses will be planned to evaluate robustness. Fifth, intervention progression, heart rate monitoring, and standardized warm-up and cool-down procedures will improve intervention fidelity and safety.

The study also has limitations. The trial will be conducted at a single center and will include only healthy female college students aged 18–22 years, which may limit generalizability to male students, older adults, patients, or athletes. The intervention period will last 8 weeks, and long-term follow-up is not planned in the current protocol; therefore, persistence of training effects will remain uncertain. The study focuses on knee muscle strength and dynamic balance rather than actual injury incidence. In addition, future studies may incorporate advanced evaluation frameworks such as feature fusion and machine learning into outcome assessments to improve the precision of functional ability measurements (46).

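### The itemised training does not fit the stated 60-min session, and the share of the URT programme given to T+URT is not fixed, so the contrast with URT may mix combination with added training

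*Protocol article*

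**What the plan says.** Four parts of the Methods fix session time and content.

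- **Interventions:** "All groups will train for 8 weeks, three sessions per week, 60 min per session". Also: "Each session will include a standardized 10-min warm-up and a standardized 10-min cool-down".
- **Tai chi Chuan group, Table 3, weeks 5–8:** "Continuous practice of the full 24-form routine, approximately 8 min per set, 7–8 sets per session, with 1-min rest intervals". The text above the table adds that "the present study adopts a protocol of 7–8 sets per session, with a total training volume of approximately 60 min". In weeks 1–2 Table 3 teaches only the first 12 movements; the full routine comes in weeks 3–4.
- **Unstable resistance training group, Table 4:** four exercises per phase in weeks 1–4, each at "30 s per set, 3 sets, 60-s rest between sets". Weeks 5–8 have three movements at "20 s static squats per set or 15 repetitions per set; 3 sets per movement; 60-s rest between sets".
- **Combined intervention group:** participants "will complete 30 min of Tai Chi Chuan followed immediately by 30 min of unstable resistance training during each 60-min session". The Tai Chi half is 3–4 sets of the whole 24-form routine, with no phasing by week. The resistance half consists of the exercises of the current URT phase; no number of sets is given, and no reduction is mentioned.

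The main hypothesis (Objectives and hypotheses) is that T+URT improves strength and balance more than either single programme. The Discussion goes further and says the trial will show whether the combination "yields synergistic effects on knee function and dynamic balance in young sedentary women".

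**The concern.** The article prints sets, rests and minutes for each arm, and they cannot all be followed in one 60-min session. Instructors would have to decide which instruction gives way, and the document does not say which.

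The consequence for inference lies in the contrasts with T+URT. If that arm does all the URT sets and Tai Chi as well, a benefit over URT may come from the combination or simply from more training, and no analysis can separate the two after delivery. The TCC contrast has its own imbalance. Unless the plan says which contrasts are meant to be equal in amount, the reader cannot tell what a positive or null result means.

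**Working it through.** **Inputs.** All come from the sections cited above, except two assumptions. (a) A 15-repetition set lasts 30–60 s: the URT section equates 30 s with about 12–15 repetitions, and the upper end is assumed. (b) One-sided exercises are counted once, or on both legs as a variant. Set-up and instruction time are not itemised and are not counted.

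**1. Time available.** 60 − 10 − 10 = 40 min. Nominal time is equal in all arms: 8 weeks × 3 sessions × 60 min = 24 h.

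**2. TCC, weeks 5–8.** The article's figure of about 60 min is reproduced by set time alone: 7 × 8 = 56 min and 8 × 8 = 64 min. With the prescribed rests (sets × 8 + (sets − 1) × 1):
- 7 sets: 56 + 6 = 62 min
- 8 sets: 64 + 7 = 71 min
- with warm-up and cool-down: 82–91 min

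Four sets take 32 + 3 = 35 min and five take 40 + 4 = 44 min, so at most four fit in 40 min.

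**3. URT.** Time = work + rests. The rests may be counted within each exercise only, or after every set.
- Weeks 1–4, work: 4 × 3 × 30 s = 6 min. Rests: 8 to 12 min. Total 14–18 min.
- Weeks 5–8, work: 3 × (20 + 30 + 30) s = 4 min up to 3 × (20 + 60 + 60) s = 7 min. Rests: 6 to 9 min. Total 10–16 min.
- Both legs, weeks 1–4 (6 exercise-sides): work 9 min, rests 12 to 18 min. Total 21–27 min.
- Both legs, weeks 5–8 (4 exercise-sides): work 5.5 to 10 min, rests 8 to 12 min. Total 13.5–22 min.

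Of the 40 min, 22–30 min are unaccounted for with one side per exercise, and still at least 40 − 27 = 13 min with both legs.

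**4. T+URT.** As stated: 30 + 30 = 60 min, or 80 min with warm-up and cool-down. Itemised, Tai Chi is 3 × 8 + 2 = 26 to 4 × 8 + 3 = 35 min if the TCC rest interval is carried over. The URT list fits in the 30-min half under every variant in step 3 (maximum 27 min). Adding the full list, one side per exercise:
- weeks 1–4: 26 + 14 = 40 to 35 + 18 = 53 min
- weeks 5–8: 26 + 10 = 36 to 35 + 16 = 51 min

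**5. Itemised training in weeks 5–8, without warm-up and cool-down, if T+URT does every listed URT set.**

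| Arm | Tai Chi (min) | URT (min) | Total (min) |
|---|---|---|---|
| TCC | 62–71 | 0 | 62–71 |
| URT | 0 | 10–16 | 10–16 |
| T+URT | 26–35 | 10–16 | 36–51 |

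T+URT then exceeds URT by the whole Tai Chi part and falls short of TCC. With both legs T+URT reaches at most 35 + 22 = 57 min, still below 62. No such comparison with TCC is possible for weeks 1–4, because Table 3 gives no number of sets there.

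**6. Content by week.** T+URT is asked for the whole routine in its Tai Chi half, while Table 3 has TCC learning only its first half in weeks 1–2.

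**The case against.** The strongest reply is that the arms are time-matched by design: every arm has the same stated hour, and the 30 + 30 split suggests that T+URT is meant to receive part of each programme. A fuller intervention manual, which the Quality control section mentions, may give the sets. This stands in part. The stated time is equal; only the itemised content differs. The manual cannot remove the conflict, though, because the contradictory figures are printed in the article.

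Several stronger readings are tempting and are not supported:

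- **T+URT is prescribed the full URT programme.** The Combined intervention group section names exercises but no number of sets. Full dosing is a plausible reading, helped by the timing, and is not stated text.
- **The imbalance favours T+URT throughout.** It can do so only against URT.
- **If 60 min is enforced, T+URT gets nearly all of both programmes.** This caps TCC at four sets but leaves T+URT uncapped. With the same 40 min split equally (20 + 20), two Tai Chi sets fit (17 min), half of TCC's four. With an unequal split, three sets plus the URT list take 36–42 min in weeks 5–8 and 40–44 min in weeks 1–4, so they fit only under some variants.
- **Four Tai Chi sets overrun the 30-min half by 5 min.** The 1-min rest is stated for TCC only; without it four sets take about 32 min, which is rounding.
- **Any instructor choice becomes a major deviation and makes the per-protocol set arbitrary.** The Adherence section requires that the change be unapproved and able to affect outcomes systematically, and the per-protocol analysis is only a sensitivity analysis.
- **Without an arm lacking both components the trial fails.** Superiority over each single programme, which is the stated hypothesis, can be tested with three arms. Only the synergy wording goes beyond the design.

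**Conclusion.** The conflict in session time holds on the printed figures. Against 40 min available, TCC in weeks 5–8 needs 62–71 min (56–64 even without rests) and T+URT is given 60 min, while the URT list leaves at least 13 min unexplained. The overrun concerns TCC and T+URT; the URT list fits. The demand for the whole routine in T+URT also sits badly with the staged learning in Table 3.

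The consequence for the contrasts is conditional. If T+URT does all sets of the current URT phase, an advantage over URT cannot be separated from 26–35 min of additional Tai Chi per session. Against TCC in weeks 5–8 the itemised amount is lower in T+URT (36–51 against 62–71 min; T+URT spans 36–53 min over all weeks). The URT times depend on how rests, repetition speed and one-sided exercises are counted, but every variant fits inside 30 min and below 40. Confidence is high for the session-time conflict and lower for the difference in dose, because T+URT's number of sets is not stated.

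**What to change.** Before the first session:

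1. Reconcile the sections Interventions, Tai chi Chuan group (Table 3), Unstable resistance training group (Table 4) and Combined intervention group, so that each arm's content adds up to its stated session length. Say whether warm-up and cool-down lie inside the 60 min, and how T+URT is taught the routine in weeks 1–2.
2. State the sets of each component that T+URT receives, relative to TCC and to URT.
3. Declare each contrast, T+URT against URT and T+URT against TCC, as time-matched or add-on.
4. In the Discussion, replace the claim about synergistic effects with one that T+URT is greater than each single programme as delivered.

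Which doses are right is for the investigators. The cost is amendment wording and the ethics review that the Protocol amendments section already requires; the wording itself needs no extra staff or tests. Once sessions have been delivered, analysis cannot repair the ambiguity.
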